### Outcomes

2.5.

Professional assessors will observe primary and secondary outcomes in participants at four time points: baseline (T1), after 4 weeks of treatment (T2), after 8 weeks of treatment (T3), and 4 weeks after the end of treatment (T4) (Table 1). To ensure the quality of scale assessments and minimize inter-rater variability, assessors will undergo unified standardized training based on a pre-established operation manual before the study begins. Only after passing the training will, they be allowed to perform assessments. Each scale assessor will be responsible for only part of the assessment tasks and will be unaware of the participants’ group assignments. They will also not be involved in the intervention process or the final data statistical analysis.

**Table 1. t0001:** Trial implementation schedule.

	Study period					
	Enrollment	Allocation	Treatment phase			Follow-up
Timepoint	−1 week		0 day	4 week	8 week	12 week

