#### Primary outcomes

2.5.1.

The change in LDL-C from baseline to 8 weeks after intervention.

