### Sample calculation

2.7.

The sample size for this study was calculated using G*Power 3.1.9.7 software based on existing research on moxibustion for treating hyperlipidemia. According to previous trial results [37], the LDL-C levels after intervention in the moxibustion group and the control group were 4.41 ± 0.52 mmol/L and 3.72 ± 0.43 mmol/L, respectively. With a two-tailed test value of α = 0.05 and a power of 0.95, the sample size per group was calculated to be *n* = 66. Considering a 20% dropout rate, the required sample size per group is 79, resulting in a total required sample size of 158 for this study.

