#### Clinical observation outcomes

2.8.2.

Missing values will be imputed using multiple imputation methods. Linear mixed models will be used to analyze data from the four measurement time points to compare group effects, time effects, and interaction effects on outcome indicators between the two groups. The model will include group, time, and the group × time interaction as fixed effects, with the subject set as a random intercept to account for the inherent correlation in repeated-measure data. The model will include variables that were unbalanced between groups at baseline as covariates to correct for the impact of baseline differences on treatment effect estimates and ensure the robustness of the results. If a significant interaction is detected, the Bonferroni corrections post-hoc test will be employed to further determine its significance, with the significance level set at *p* < 0.05 for a two-tailed test.

Given that the inclusion criteria of this study do not restrict cognition and emotional state, the study may be insufficiently sensitive to detecting improvements induced by the intervention. Based on this, we will conduct subgroup analyses focusing on subgroups with mild cognitive impairment (MoCA score < 26), depressive symptoms (HAMD score > 7), and anxious symptoms (HAMA score > 7), respectively. We will analyze the impact of the intervention on cognitive and emotional scores separately within these subgroups to further identify the populations that benefit from the intervention and to more comprehensively evaluate the potential benefits of the intervention.

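### The primary contrast, LDL-C change to week 8, is not designated as the primary test and sits behind a four-visit interaction gate and a Bonferroni step

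*Protocol article*

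**What the plan says.** Section 2.5.1 gives a single primary outcome: "The change in LDL-C from baseline to 8 weeks after intervention". In a two-arm trial that is one between-group contrast.

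Section 2.7 plans for one comparison of two groups: "With a two-tailed test value of α = 0.05 and a power of 0.95". It makes no allowance for a gate or for several comparisons.

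Section 2.8.2 gives one analysis for all clinical outcomes: "Linear mixed models will be used to analyze data from the four measurement time points to compare group effects, time effects, and interaction effects". On the model it says: "The model will include group, time, and the group × time interaction as fixed effects". Under section 2.5 the four visits are baseline, weeks 4 and 8 of treatment, and four weeks after treatment ends, so the interaction test has 3 degrees of freedom and includes an off-treatment visit. Follow-up is then conditional: "If a significant interaction is detected, the Bonferroni corrections post-hoc test will be employed to further determine its significance". Testing there is two-sided at 0.05.

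The article does not identify the week-8 contrast as the test that decides the primary question. It also does not say how many comparisons the Bonferroni step covers.

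**The concern.** A trial with one pre-specified contrast needs neither an omnibus gate nor a multiplicity correction for it. The rule in section 2.8.2 asks the week-8 difference to clear two extra hurdles: a 3-df test that spends part of its sensitivity on weeks 4 and 12, and a stricter threshold. For the same contrast, this route can never have more power than a direct test at 0.05. A real week-8 effect could therefore be reported as negative because the overall interaction missed 0.05, or because week 8 missed a corrected threshold that a single primary contrast does not require. The test that the sample size assumes is also not the test that the analysis section describes.

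A second, smaller matter is that group, time and interaction effects are listed side by side. The group main effect averages in the pre-treatment visit, so it is not the primary quantity, and nothing in the text says that it does not decide efficacy.

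**Working it through.** **1. The plan's own figure.** Inputs from section 2.7: post-treatment LDL-C of 4.41 (SD 0.52) and 3.72 (SD 0.43) mmol/L, two-sided 0.05, power 0.95, 66 per group, 79 after dropout.

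- Pooled SD = √[(0.52² + 0.43²)/2] = 0.477; d = 0.69/0.477 = 1.446.
- n per group = 2(1.960 + 1.645)²/1.446² = 12.4, so 13 (14 with the t distribution). The stated 66 is not reproduced.
- Conversely, 66 per group at 95% power corresponds to d = √(2 × 3.605²/66) = 0.63, about 0.30 mmol/L at SD 0.477.

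Section 2.7 therefore supports two very different effect sizes, and both are carried below. Completers per arm: 79 × 0.8 ≈ 63.

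**2. The gate.** Assume the random-intercept model of section 2.8.2, complete data and 63 per arm. The error df are 3 × (126 − 2) = 372. Let s² be the within-subject error variance of the group difference at one visit, and D the true week-8 effect.

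- Direct contrast (week 8 minus baseline): δ = D/(s√2). Power of 95% needs δ = 3.61, so δ² = 13.06.
- Interaction noncentrality: λ = Σ(Δₜ − Δ̄)²/s², where Δₜ is the group difference at visit t. The critical F on (3, 372) df is 2.63.
- Effect 0, ½, 1, ½ of D: the sum of squares is 0.5D², so λ = 0.5 × 2 × 13.06 = 13.1. The gate passes 87% of the time.
- Effect 0, 1, 1, 1 of D: the sum of squares is 0.75D², so λ = 0.75 × 2 × 13.06 = 19.6. The gate passes 97% of the time.

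The between-subject variance cancels from both tests, so once direct power is set at 95% these results do not depend on the correlation.

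**3. The Bonferroni step.** With three change contrasts the threshold is 0.05/3 = 0.0167, and power for week 8 alone falls to about Φ(3.61 − 2.40) ≈ 89%. Requiring both the gate and this threshold (by simulation) gives 85% for the half/full/half shape and 88% for the sustained shape, against 95% for the direct test.

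**4. Other effect sizes.** Simulation of the same change contrast, 66 per arm, Bonferroni over four comparisons, several effect shapes:

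| Week-8 d | Correlation | Direct test | Gate plus Bonferroni |
|---|---|---|---|
| 0.63 | 0.5 | 95% | 85–86% |
| 0.63 | 0.7 | 99.7% | 98% |
| 0.5 | 0.5 | 82% | 61–64% |
| 0.5 | 0.7 | 96% | 86–88% |
| 0.4 | 0.5 | 63% | 38–41% |
| 0.4 | 0.7 | 84% | 64–67% |
| 1.446 | either | about 100% | about 100% |

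With three comparisons, correlation 0.5 and d of 0.4 to 0.5, the gated figures are 62–67% (d = 0.5) and 40–44% (d = 0.4). Across three or four comparisons the loss there is 15 to 25 points, about 20 in the middle.

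**5. No true effect.** Gate plus Bonferroni rejects for the week-8 change about 1% of the time, against 5% for a direct test. If a significant group main effect or a significant interaction could each count as success, the error would be about 1 − 0.95² = 9.75%; simulation gives just under 10%.

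**The case against.** Several points on the other side are fair.

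- **The contrast is estimated.** With group × time over four visits, the group-by-week-8 coefficient is exactly the between-group difference in change. Naming the decisive coefficient and counting the Bonferroni comparisons are details often left to an analysis plan. That stands for those details. It does not cover the gate and the correction, which the article itself writes down: an analysis plan that tested week 8 directly would depart from them.
- **The text does not say what happens to week 8 if the interaction is not significant.** Follow-up only after a significant interaction is the natural reading, but it is a reading.
- **The loss depends on assumptions.** The article gives no within-subject correlation, effect shape or number of comparisons. At its own quoted effect nothing is lost, though those means do not lead to 66 per group and so are a weak reassurance.
- **Omnibus testing followed by corrected comparisons is conventional.** It neither biases the estimate nor inflates false positives for the week-8 contrast.

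Two stronger readings are tempting and should not be made. First, a reader might infer that power falls far below 85% even where the direct test has 95%. Such figures appear only if the post-hoc test is also switched from change to the raw week-8 difference. That comparison has lower power even with no gate or correction, and the article does not prescribe it. Second, a reader might infer that type I error doubles. That needs a success rule under which a group main effect or interaction is enough, and no section states one. Listing the three effects is ordinary mixed-model description.

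**Conclusion.** The point holds as a mismatch between the primary outcome and the written testing rule. Section 2.5.1 fixes one contrast and section 2.7 plans one unadjusted test, while section 2.8.2 places follow-up behind a 3-df interaction and then corrects it.

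The like-for-like cost is about 7 to 10 points of power when the direct test has 95% (63 per arm, three change contrasts, random-intercept model). It is about 20 points for smaller effects at correlation 0.5, and nothing at d of about 1.45. The direction is certain under any assumption; the size is not. The rule is conservative, so the risk is a missed effect and not a false claim. The near-10% type I error is conditional on a reading that the article neither adopts nor rules out. This should be fixed, but it does not invalidate the design.

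**What to change.** Add to section 2.8.2, before any unblinded look at the data:

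> The primary test is the between-group difference in LDL-C change from baseline to week 8 (T3), estimated as one contrast from the mixed model at two-sided alpha 0.05 and reported with a 95% confidence interval. It is performed regardless of the overall interaction test and without Bonferroni correction.

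Then make the T2 and T4 contrasts secondary, keep Bonferroni for those and state the number of comparisons. Add that the group and time main effects do not decide efficacy.

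The cost is a few sentences of wording. The model, data, visits and sample size do not change.

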#### Correlation analysis

2.8.4.

Spearman correlation analysis will be employed to explore the correlations between gray matter volume, gut microbiota, TMAO levels, and primary and secondary outcomes, respectively, in order to preliminarily reveal the potential mechanisms underlying the infrared moxibustion intervention effects. Bonferroni correction will be applied to adjust for multiple comparisons.

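### Section 2.8.2 looks for the patients who benefit by testing inside three symptomatic subgroups, but states no treatment-by-subgroup interaction and no correction across those tests

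*Protocol article*

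**What the plan says.** Section 2.8.2 (Clinical observation outcomes) first sets out the general model for the repeated clinical measures: "The model will include group, time, and the group × time interaction as fixed effects", with a random intercept per subject. On multiplicity it says: "If a significant interaction is detected, the Bonferroni corrections post-hoc test will be employed to further determine its significance". Tests in this section are two-sided at 0.05.

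The next paragraph introduces the subgroups. Eligibility does not depend on cognition or mood, so the authors expect that "the study may be insufficiently sensitive to detecting improvements induced by the intervention". They therefore name "subgroups with mild cognitive impairment (MoCA score < 26), depressive symptoms (HAMD score > 7), and anxious symptoms (HAMA score > 7), respectively". The method and its purpose follow in one sentence: "We will analyze the impact of the intervention on cognitive and emotional scores separately within these subgroups to further identify the populations that benefit". The same sentence adds a second, broader aim of assessing possible benefit more fully.

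Elsewhere the article is explicit about multiplicity. Section 2.8.3 uses family-wise error control and Bonferroni for the MRI analyses, and section 2.8.4 says of the correlations: "Bonferroni correction will be applied to adjust for multiple comparisons". Section 2.5.3 labels microbiota, TMAO and MRI as exploratory. The subgroup analyses carry no such label, and the limitations in the Discussion do not mention them.

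**The concern.** Saying which population benefits is a comparative claim: the effect is larger in these patients than in the others. A test confined to one subgroup answers a different question, namely whether there is an effect in that subgroup. A significant result there is compatible with the same effect everywhere, and a non-significant one may only reflect a small subset. The direct evidence is the difference between effects, that is, a treatment-by-subgroup interaction, and section 2.8.2 does not specify one.

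The second limb is the number of tests. The three subgroups can overlap, each may be tested on more than one score, and no adjustment across them is stated.

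At stake is a responder claim about cognition or mood. The Discussion already anticipates improvement in both, so one significant subgroup could easily be reported as the population to treat.

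**Working it through.** The plan gives no test count, error rate or power for these analyses, so there is no figure of its own to reproduce.

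**Inputs from the document.** Three subgroups; two-sided 0.05 (section 2.8.2); 1:1 allocation (section 2.2); 66 per group before and 79 after the dropout allowance (section 2.7, used here only as arm sizes); ITT (section 2.8) with multiple imputation (section 2.8.2).

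**Assumptions.** Share of patients in a subgroup 20% to 50%; true standardised effect d = 0.3 to 0.5; correlation among scores 0 to 0.6; a simple two-arm comparison at one time point.

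**1. Which interaction is specified?** The model has group, time and group × time. The Bonferroni step is triggered by a significant interaction, and group × time is the only one defined. It therefore covers follow-up comparisons within a model, not the set of subgroup tests.

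**2. Does within-subgroup significance identify responders?** Give every patient the same true effect. Let P1 be the power in the subgroup and P2 the power in its complement (t-test, 66 per arm in total). The chance that the two disagree is P1(1 − P2) + P2(1 − P1).

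| d | Share | n per arm (subgroup / complement) | P1 | P2 | Disagree |
|---|---|---|---|---|---|
| 0.3 | 20% | 13 / 53 | 0.114 | 0.334 | 0.372 |
| 0.3 | 30% | 20 / 46 | 0.152 | 0.296 | 0.358 |
| 0.3 | 50% | 33 / 33 | 0.225 | 0.225 | 0.348 |
| 0.5 | 20% | 13 / 53 | 0.232 | 0.722 | 0.619 |
| 0.5 | 30% | 20 / 46 | 0.338 | 0.660 | 0.552 |
| 0.5 | 50% | 33 / 33 | 0.516 | 0.516 | 0.499 |

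Disagreement runs from about 35% to 62% although nobody responds differently. It can mislead in both directions. At d = 0.5 and a 50% share, the subgroup alone is significant with probability 0.516 × 0.484 = 0.25. At d = 0.5 and a 20% share, the complement alone is significant with probability 0.722 × 0.768 = 0.55.

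**3. False positives across the tests.** The narrow reading tests each subgroup on its own scale, giving 3 tests. The widest tests each subgroup on MoCA, HAMD and HAMA, giving 3 × 3 = 9.

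- 3 tests: 1 − 0.95³ = 0.143
- 9 tests: 1 − 0.95⁹ = 0.370

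These treat the tests as independent. A null simulation with overlapping subgroups and correlated scores (66 per arm, shares and correlations as above) gave about 13% to 15% for 3 tests and 26% to 36% for 9. Bonferroni thresholds would be 0.05/3 = 0.0167 and 0.05/9 = 0.0056.

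**4. What the subgroups and the interaction can detect.** At 80% power and two-sided 0.05, the detectable within-subgroup d is about 2.8 × √(2/m), with m patients per arm. A 30% share of 79 per arm (ITT, all patients analysed) gives m ≈ 24 and d ≈ 0.81. A 30% share of 66 gives m ≈ 20 and d ≈ 0.89. The detectable difference between subgroup and complement, with 24 and 55 per arm, is 2.8 × √(2/24 + 2/55) = 2.8 × 0.346 ≈ 0.97. Using 79 per arm, shares of 20% and 50% give within-subgroup values of about 1.00 and 0.63, and interaction values of about 1.11 and 0.89. Repeated measures or covariate adjustment may improve on these.

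**The case against.** The strongest defence is the plan's own rationale. Patients who score normally at entry have little room to improve, so a whole-sample comparison may dilute an effect on cognition or mood. Asking whether symptomatic patients improve is legitimate, and a within-subgroup estimate answers it without an interaction or a complement. That stands, and it is why the within-subgroup analyses should be kept. It does not extend to the further step of identifying who benefits.

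Two stronger readings are tempting, and the document supports neither.

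- A reader might infer that nine uncorrected tests are planned. The text gives no count. Each subgroup is named by its own scale, so three matched tests are an equally natural reading. The missing correction is read from silence in a condensed article whose neighbouring sections do correct. What can be said is that no correction across these tests is stated and that the one in section 2.8.2 is tied to a different interaction.
- A reader might infer that patients outside the subgroups will not be analysed at all. The article does not say so. It only describes no comparison with them.

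Cut-offs instead of the continuous score are also defensible: they are prespecified and easy to interpret, and the lost information is a trade-off, not an error. Finally, these are analyses of secondary outcomes, so the impact is limited.

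**Conclusion.** The point holds in a limited form. Section 2.8.2 fixes both a method (separate analysis within subgroups) and an inference (which populations benefit), and the method cannot support the inference. This is stated in the protocol, so it is more than a detail left to an analysis plan, and it would remain even if every subgroup test were corrected.

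The size of the multiplicity problem depends on how the text is read: about 14% for three tests and at most 37% for nine. The 35% to 62% disagreement rate and the detectable effects rest on assumed effect sizes and subgroup shares, because the plan gives no expected prevalence. They show how unreliable the inference is and do not predict this trial's results. The LDL-C primary analysis, the sample size and the main conclusion are unaffected.

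**What to change.** 1. Keep the within-subgroup treatment effects, with 95% CIs, and label them exploratory estimates of effect in symptomatic patients.
2. For any statement about who benefits, extend each score's full-sample mixed model with a treatment × baseline-status term (with time, and the lower-order terms), using either the baseline score or the prespecified cut-off. Report the interaction estimate with its 95% CI, Bonferroni-adjusted over the interactions tested, and state how many there are.
3. Show the effects descriptively on both sides of each cut-off as the plan defines it: MoCA < 26 against ≥ 26, HAMD > 7 against ≤ 7, HAMA > 7 against ≤ 7.
4. Note that ceiling or floor effects can contribute to an interaction on these scales, since patients near the healthy end cannot improve much.
5. Remove the wording about identifying who benefits unless the interaction supports it.

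The cost is wording and a few model terms, on data already being collected. The downside is low power: at a 30% share, only a difference in effect of roughly one standard deviation would be detectable before the Bonferroni adjustment, so fewer responder claims will be possible. The change is best made before unblinding, so that it cannot be seen as driven by the data.

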#### MRI analysis

2.8.3.

To explore whether baseline brain structure is correlated with clinical phenotypes, voxel-based morphometry (VBM) will be employed to analyze the correlation between baseline gray matter volume and primary and secondary observed outcomes across all participants on a whole-brain scale. Age, sex, years of education, and total intracranial volume will be included as covariates in the regression model for control. Multiple comparison correction will be performed at the whole-brain voxel level using family-wise error rate (FWE), with a voxel-level P_FWE_ < 0.05 considered statistically significant.Based on the brain regions showing significant correlations in analysis (1), gray matter volume in these regions was extracted for each participant to construct regions of interest (ROIs). A two-sample *t*-test was used to compare differences in gray matter volume between the two groups within the aforementioned ROIs, with age, gender, years of education, and total intracranial volume included as covariates. The Bonferroni method was used for multiple comparison correction.

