**Patient and methods:**

This study will recruit 158 patients with mild hyperlipidemia and randomly assign them to either a genuine infrared moxibustion group or a sham infrared moxibustion group. The intervention will be administered twice weekly for a total of 8 weeks. Blood lipid levels, Montreal Cognitive Assessment scores, Hamilton Depression Rating Scale scores, Hamilton Anxiety Scale scores, and Pittsburgh Sleep Quality Index scores will be compared between the two groups before treatment, and at 4, 8, and 12 weeks post-treatment. Additionally, changes in gut microbiota, the gut microbiota metabolite trimethylamine N-oxide (TMAO), and brain gray matter volume will be detected and compared between the two groups before treatment and at 8 weeks post-treatment (See Graphic Abstract).

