However, this study has several limitations. Firstly, the inclusion of various types of hyperlipidemias, including hypercholesterolemia, hypertriglyceridemia, and mixed hyperlipidemia, results in a relatively complex distribution of disease types. Nevertheless, this study can preliminarily establish the efficacy of infrared moxibustion for HLP. Future research can build upon these findings to focus on the effects of infrared moxibustion on different types of HLP. Secondly, the sample size of this study was calculated based on LDL-C, and its power for whole-brain neuroimaging analysis was insufficient. Therefore, it is necessary to conduct large-sample studies in the future for further verification. Furthermore, the association between gut microbiota and lipid metabolism is time-dependent and complex. Short-term interventions may lead to asynchronous changes between the two. The correlation analysis in this study can only preliminarily verify their association. Future studies with longer intervention periods and follow-up durations are needed to clarify the long-term causal relationship between them.

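### The between-group gray matter test uses neither baseline volume nor change and names no time point, and it runs only in regions that pass an underpowered baseline screen.

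*Protocol article*

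**What the plan says.** **Scans.** Table 1 and section 2.5.3.3 schedule MRI at baseline and week 8.

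**Aim.** The abstract says that "brain gray matter volume will be detected and compared between the two groups before treatment and at 8 weeks post-treatment". The subject of that sentence is changes in the listed measures, gray matter volume among them. The introduction hypothesises that treatment lessens brain atrophy.

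**Screen (2.8.3, first analysis).** Voxel-based morphometry is used to "analyze the correlation between baseline gray matter volume and primary and secondary observed outcomes across all participants on a whole-brain scale". On the threshold: "Multiple comparison correction will be performed at the whole-brain voxel level using family-wise error rate (FWE"), at a voxel-level value of 0.05.

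**Treatment comparison (2.8.3, second analysis).** "Based on the brain regions showing significant correlations in analysis (1), gray matter volume in these regions was extracted for each participant". A two-sample t-test then serves to "compare differences in gray matter volume between the two groups within the aforementioned ROIs". Its adjustment set is four variables (age, gender, education and intracranial volume), and Bonferroni correction is applied.

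**Limitation.** The discussion says of the sample size that "its power for whole-brain neuroimaging analysis was insufficient".

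**The concern.** The question is whether treatment alters brain volume over 8 weeks. To answer it, the analysis needs each patient's starting volume, either as a covariate or through a change score. Section 2.8.3 gives a covariate list without it and does not say which scan supplies the volume. If week-8 volume alone is compared, the contrast is still unbiased by randomisation, but stable differences between people stay in the error term although the scan that would remove them has been collected.

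The second problem is where the test is run. Regions enter only if their baseline volume correlates with a clinical measure at a strict whole-brain threshold. If none passes, the section offers no treatment comparison. A region that responds to treatment but is uncorrelated at baseline is never tested. One of the trial's three stated mechanisms (microbiota, TMAO, brain volume) could then go unanswered after every patient has been scheduled for two scans.

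**Working it through.** **Is the contrast supplied elsewhere?** No.
- Section 2.8.2 fits mixed models to data from four time points; MRI has two.
- Section 2.8.4 is a Spearman analysis of associations, not a comparison of arms.
- The processing steps in 2.5.3.3 include none that pairs a patient's two scans.

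**Inputs for the precision check.** The documents give no MRI sample size or power figure, so there is none to reproduce.
- Patients: 79 per arm less 20% dropout (section 2.7) = 63.2, taken as 63.
- Two-sided alpha 0.05 and 80% power: multiplier 1.96 + 0.84 = 2.80. One region, before Bonferroni.
- r = correlation of baseline and week-8 regional volume after the planned covariates. Assumed 0.80 to 0.95; not in the documents.
- Effects in units of the week-8 SD after those covariates, with equal variance at both scans.

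**Formulas for the detectable effect**
- Week-8 only: 2.80 × sqrt(2/63) = 0.50 SD
- Change score: 0.50 × sqrt(2(1 − r))
- ANCOVA on baseline: 0.50 × sqrt(1 − r²)
- SE of ANCOVA relative to change score: sqrt((1 + r)/2)

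| r | Week-8 only | Change score | ANCOVA | Residual variance, ANCOVA vs week-8 only | SE, ANCOVA vs change |
|---|---|---|---|---|---|
| 0.80 | 0.50 | 0.32 | 0.30 | 0.36 | 0.95 |
| 0.90 | 0.50 | 0.22 | 0.22 | 0.19 | 0.97 |
| 0.95 | 0.50 | 0.16 | 0.16 | 0.098 | 0.99 |

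With 66 per arm, the pre-dropout number in section 2.7, the pattern is the same: 0.49 SD for week-8 only against 0.29, 0.21 and 0.15 SD for ANCOVA. For a true effect of 0.2 SD, power rises from 21% to 48%, 75% and 96%.

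**How hard is the screen to pass?** Assume that voxel-level FWE 0.05 corresponds to |T| of about 5 (range 4.5 to 5.5; not in the documents). With four covariates, df = N − 6 and the critical correlation is T/sqrt(T² + df).
- N = 158: 5/sqrt(25 + 152) = 0.38
- N = 132 (2 × 66): 5/sqrt(25 + 126) = 0.41

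By Fisher's z, the chance that a given voxel with true correlation 0.3 passes is 1 − Φ[(atanh(critical r) − atanh(0.3)) × sqrt(N − 7)]. This gives 15% (N = 158) or 9% (N = 132), and 3% to 28% over the threshold range. With true correlation 0.2 and |T| = 5 it is about 1% or less. These are single-voxel figures; a spatially extended association has a better chance that some voxel passes.

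**The case against.** **Change may be what was meant.** The abstract speaks of changes and both scans are taken, so the differences in section 2.8.3 can be read as differences in change. A reader might infer that the plan simply discards the baseline scan and is nearly blind to an effect. The documents do not establish that: under the change reading almost all of the precision loss disappears. What stands is that 2.8.3 does not say so, while it does spell out the test and its covariates.

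**A t-test with covariates.** A reader might call this a contradiction. It is only a label: with four covariates and the SPM12/CAT12 software named, a covariate-adjusted two-group linear model is plainly intended.

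**The screen is legitimate.** A reader might infer that choosing regions by correlation biases the group contrast. It does not, provided that the clinical measures in the screen are also baseline values, as its stated purpose suggests: selection on pooled baseline data is independent of allocation. The objection is to its reach, not its validity.

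**Article format and status.** A fallback rule could sit in a fuller document, the endpoint is labelled exploratory, and low power is disclosed. This lowers the severity. But the disclosure does not say that the treatment comparison itself depends on the underpowered step, and the article fixes the test, covariates, region rule and correction explicitly.

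**Conclusion.** The point holds as a gap in the specification with a free remedy. As written, the only between-group gray matter test includes neither baseline volume nor change and names no time point, which does not match the abstract's aim.

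The size depends on the reading. For a week-8-only test, and an assumed correlation of 0.80 to 0.95, baseline adjustment lowers the detectable effect from about 0.50 to 0.30 to 0.16 SD (one region, 63 per arm, 80% power, before Bonferroni). Against change scores, ANCOVA reduces the standard error by only about 1 to 5%, and what remains is to reconcile the abstract with section 2.8.3.

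Secondarily, the comparison depends on a screen whose insufficient power the protocol concedes, so an empty region set is plausible, though not certain. No primary or clinical secondary conclusion rests on this analysis, so the severity is modest.

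**What to change.** 1. In section 2.8.3, define the between-group comparison as an ANCOVA of week-8 regional gray matter volume on group, with baseline volume of the same region added to age, sex, years of education and total intracranial volume. Make the abstract and 2.8.3 agree that this is the comparison of change.
2. Before unblinding, fix a short region list and run this ANCOVA in it whatever the screen shows, with Bonferroni over the list. The choice is the sponsor's, from its own rationale: the introduction and discussion mention hippocampus and entorhinal cortex, and the discussion's acupuncture study reports gray matter change in the superior frontal gyrus, cerebellar posterior lobe and right precentral gyrus.
3. Keep the screened regions as an additional exploratory set, analysed with the same model.

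**Cost.** Wording only. Both scans are already scheduled and no patient, visit or measurement is added. The one burden is committing to a region list in advance.
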